### 2.12. Randomization and Blinding

Patients will be randomized in a 1:1 ratio after meeting the study inclusion and exclusion criteria. In the control group, patients will receive standard nutritional recommendations, whereas in the intervention group, they will follow a dietary strategy based on partial enteral nutrition combined with an exclusion diet, which has been shown to be effective in inducing remission, promoting mucosal healing, and serving as a rescue therapy for patients with inadequate response to biologic treatments.

Patients in the intervention group will be required to maintain this dietary strategy for 12 weeks, with structured follow-up visits at 6, 12, 24, and 48 weeks. Subsequently, patients should continue with the maintenance phase starting from week 13 onwards. Nutritional intake will be adjusted to ensure a balanced provision of macronutrients and essential micronutrients, prioritizing the inclusion of key substrates for short-chain fatty acid production while avoiding foods and additives with potential pro-inflammatory effects.

Simple randomization will be computer-generated and conducted by a member of the research team at the study site. Due to the nature of the intervention, neither patients nor research or medical staff will be blinded. Group assignment will be disclosed to patients at the moment of their participation acceptance.

Furthermore, to minimize the risk of bias, the clinicians from the Gastroenterology Department responsible for performing imaging assessments, as well as the translational researchers from the Biomedical Research Institute of Murcia (IMIB) in charge of analyzing blood, urine, and stool samples, will remain blinded to the dietary allocation of the study participants.

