### 2.2. Design

This is an experimental, prospective, randomized study with matched data, including patients with CD who are either about to begin pharmacological treatment or are scheduled to have their medication changed due to an insufficient response and lack of positive disease progression. The pharmacological treatment will be prescribed based on clinical indications by the medical team at baseline and will not be influenced by whether the exclusion diet is implemented.

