### 2.11. Sample Size and Recruitment

Based on similar studies conducted primarily in pediatric populations, but also in adults [11,12], and taking into account the multiple outcomes to be obtained from the analysis of multiple variables, we estimate that, to achieve a significance level of 0.05 and a statistical power (β) of 0.8, a sample size of 48 patients per group would be required. Adjusting for a 5% dropout rate, we plan to recruit at least 50–55 patients per group to ensure the robustness of the analysis.

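### Simple randomisation does not assure the per-group numbers of section 2.11, and neither the allocation nor the named tests use the start-versus-change drug mix

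*Protocol article*

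**What the plan says.** Section 2.12 sets a 1:1 ratio and the method: "Simple randomization will be computer-generated", with someone from the site's research team carrying it out. It names no blocks, strata or minimisation factors, and the trial is open-label for patients and treating staff.

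Section 2.11 works per group. At a 0.05 significance level and 0.8 power, "a sample size of 48 patients per group would be required". After a 5% allowance for dropout, "we plan to recruit at least 50–55 patients per group to ensure the robustness of the analysis". It gives no total at which recruitment stops. Section 2.5 adds that withdrawn patients are not replaced.

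Section 2.2 describes a mixed population: patients are "either about to begin pharmacological treatment or are scheduled to have their medication changed due to an insufficient response". The drug is prescribed at baseline on clinical grounds, independently of the diet. Section 2.15 names Student's t-test, ANOVA and the chi-square test for comparisons. It also mentions multivariate models for relationships among several variables, without naming covariates.

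**The concern.** Simple randomisation fixes the total and leaves the size of each arm to chance. A requirement written per group, with no replacement of withdrawals, is therefore not secured by the allocation method, even at the top of the planned range.

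The second issue is separate and has nothing to do with arm size. All patients have their drug treatment started or changed at about the time the diet begins. Those starting and those switching after an inadequate response may well remit at different rates. If they do, the comparison carries avoidable noise unless the factor is balanced at allocation or used in the analysis. What is at stake is precision and the planned per-group size. The validity of the test is not in question.

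**Working it through.** **Inputs from the protocol.** 48 per group required, 5% dropout, at least 50–55 per group recruited (2.11); simple 1:1 allocation (2.12); no replacement (2.5).

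**Assumptions.** Recruitment stops at 110 (2 × 55). Dropout is independent and equal in both arms. A two-sided 5% test is used. The protocol does not use the word evaluable; here it means patients left after the stated dropout.

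**1. The plan's own inflation.** 48 / 0.95 = 50.5, so 51 per group, which lies inside 50–55. The lower end falls just short: 50 × 0.95 = 47.5. The base figure of 48 cannot be rederived, because 2.11 states no effect size or rates.

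**2. Arm sizes at 110.** One arm ~ Binomial(110, 0.5), with a 95% range of 45 to 65.
- P(both arms ≥ 50) = Σ C(110,k)/2¹¹⁰ for k = 50 to 60 = 70.6%, so 29.4% that an arm is below 50.
- Evaluable in an arm of size k ~ Binomial(k, 0.95). P(both ≥ 48) = Σ P(k) · P(Bin(k, 0.95) ≥ 48) · P(Bin(110−k, 0.95) ≥ 48) = 63.5%, so 36.5% that an arm is below 48.
- Fixed 55/55: P(Bin(55, 0.95) ≥ 48)² = 98.8%, so 1.2%.
- If simple randomisation is kept, both arms reach 48 evaluable with probability 82% at 115 enrolled, 90% at 119 and 95% at 123.

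**3. What unequal arms cost.** The standardised effect that gives 80% power with 48/48 is d = (1.960 + 0.842) × √(2/48) = 0.572. Power = Φ(d / √(1/n₁ + 1/n₂) − 1.960).
- 52/52: 83.1%. 47/57: 82.7%. 42/62: 81.6%.
- Averaged over simple randomisation of 104: 82.7%, a loss of 0.4 points.

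**4. Chance imbalance in the drug mix at 110.** The share of starters is not given, so a range is shown (400,000 simulations).

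| Starters | Arms differ by ≥ 10 points | ≥ 15 points |
|---|---|---|
| 20% | 19% | 5% |
| 30% | 26% | 9% |
| 50% | 30% | 11% |

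Blocking without stratification hardly changes this (19%, 25% and 29% for ≥ 10 points).

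**5. Power, separating allocation from analysis.** Assumptions: 104 patients, half starters, a 27-point effect, and remission averaged over arms as shown (20,000 simulations).

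| Remission, starters / changers | Simple, unadjusted | Simple, Mantel-Haenszel | Stratified, Mantel-Haenszel |
|---|---|---|---|
| 65% / 40% | 79.4% | 81.6% | 83.4% |
| 70% / 35% | 80.0% | 84.6% | 85.5% |
| no difference | 79.8% | 79.0% | 79.5% |

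Separate runs of the first and last columns for the two prognostic rows agree within 0.8 points. Type I error stays near 5%.

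**The case against.** Simple randomisation is valid and the least predictable method. That has value in an open-label, single-site trial where a member of the research team runs the allocation. This stands, and section 2.12 contains no misstatement.

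The recruitment figure is a floor per group and no total is fixed, so the 29% and 36% depend on stopping at 110. This also stands. Recruiting on until both arms are large enough would meet the floor, at the price of more patients (step 2).

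Several stronger readings are tempting, but the documents do not support them:
- **That the per-group targets fail at 110.** Both arms reach 50 recruited about 71% of the time and 48 evaluable about 64% of the time. The targets are not assured, but they are more likely met than missed.
- **That an uneven drug mix would bias the diet comparison.** Chance imbalance is already allowed for in the test, and type I error stays near 5%.
- **That start versus change is the dominant prognostic factor.** No section says so. The abstract describes patients not improving on conventional drugs, and the Discussion describes patients initiating biologics or JAK inhibitors. Some starters may therefore have failed earlier treatment, which would weaken the contrast.
- **That the final analysis will be unadjusted.** Section 2.15 mentions multivariate models, and covariates may be fixed in an analysis plan that is not shown. What can be said is that the comparisons named in 2.15 do not use this factor.

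**Conclusion.** The point holds as an inexpensive improvement to the design; it does not expose an error that threatens validity.

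**Arm size.** Simple allocation leaves roughly a one-in-three risk of missing the plan's own per-group number at 110 enrolled, and restricted allocation nearly removes it. The loss of power is under half a point, so what is gained is mainly that the trial delivers the numbers it states.

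**Drug mix.** The loss is one of precision. Adjustment alone brings power to about 82–84%, and stratified allocation adds about 1–2 points more. These gains rest on assumed remission rates, an assumed equal mix and an assumed 27-point effect, none of which the protocol gives. If the factor does not predict remission, there is no gain and up to about 1 point is lost.

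**What to change.** In section 2.12, replace simple randomisation by permuted blocks of randomly varying size, undisclosed to those enrolling patients, or by minimisation with a random element. Stratify by drug start versus drug change, as decided and recorded before allocation.

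In section 2.15, include that stratum in the remission analysis (Mantel-Haenszel or logistic regression) and in the models for continuous outcomes. If only one change can be made, this one brings most of the power gain.

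The cost is two sentences and a setting in the randomisation program, with no extra patients. Two limits should be accepted openly:
- Blocks make allocation slightly more predictable in this open-label, single-site trial. Random block sizes or minimisation limit this.
- Incomplete blocks in two strata can leave the arms a few patients apart, so the 1% figure is for an exact 55/55 split. An arm of 53 has a risk of about 5% of falling below 48: the chance that two such arms both reach 48 is 90.6%, and 1 − √0.906 = 0.048.

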## 2. Materials and Methods

### 2.1. Study Objectives

The primary objective of this clinical study is to determine the effectiveness and impact on body composition of implementing an ED for symptomatic remission in adult patients with active CD.

To achieve this objective, five specific aims are defined:To assess the improvement of clinical and inflammatory parameters related to the progression of the disease.To evaluate the incidence of sarcopenia through the assessment of muscle strength, function, and composition using functional tests, dynamometry, bioelectrical impedance analysis (BIA), and nutritional ultrasound.To determine the rate of improvement in the quality of life of patients and the disease remission by evaluating the Crohn’s Disease Activity Index (using the CVEII9 quality of life questionnaire and the Harvey–Bradshaw Index).To analyze the modifications in the intestinal microbiota resulting from the implementation of the ED.To examine the progression of clinical, anthropometric, analytical, and body composition parameters.

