This study presents some methodological limitations. First, the use of self-administered dietary assessment tools (PREDIMED and FFQ) introduces inherent biases, including recall bias and social desirability bias, which may compromise the accuracy of reported dietary adherence. Second, inter-individual variability in adherence to the nutritional intervention could affect the interpretation of objective outcome measures. Additionally, attrition and a relatively limited sample size may reduce the statistical power of the study, potentially limiting the ability to detect clinically meaningful differences or perform robust subgroup analyses. Residual confounding variables—such as psychological stress, levels of physical activity, and other lifestyle factors—may also influence study outcomes despite attempts at control. Finally, both inter- and intra-observer variability in ultrasound assessments, including intestinal ultrasound and quadriceps rectus femoris muscle evaluation, constitute further sources of potential measurement bias.

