**Assessments**						
Quality of life questionnaire (CVEII-9)		X	X	X	X	X
Harvey–Bradshaw activity index		X	X	X	X	X
Physical activity questionnaire (PAQ)		X			X	X
Food Frequency Questionnaire (FFQ)		X			X	X
24 h dietary recall		X	X	X	X	X
Mediterranean diet adherence questionnaire (PREDIMED)			X		X	X
Anthropometry (weight, height, BMI)		X		X	X	X
Sarcopenia screening (SARC-F)		X		X	X	X
Functional sarcopenia tests (dynamometry)		X		X	X	X
Bioelectrical Impedance Analysis (BIA)		X	X	X	X	X
Nutritional ultrasound		X		X	X	X
Blood tests, urine and stool samples		X	X	X	X	X
Intestinal imaging (MRI/intestinal ultrasound).		X			X	X
Intestinal biopsy. Optional.		X			X	X

Pre-DE: before diet exclusion. t0: baseline or initial visit. t1 (6 w): visit at 6 weeks. t2 (12 w): visit at 6 weeks. t3 (24 w): visit at 24 weeks. t4 (48 w): visit at 48 weeks.

**Table 2 jcm-14-03998-t002:** Obligatory, permitted, and prohibited foods in the exclusion diet in patients with Crohn’s disease.

Phase	Type of Food	
Phase 1 (0–6 weeks)	Obligatory	Protein-rich foods: fresh chicken breast (at least 150–200 g/day), 2 eggs/day. Carbohydrate-rich foods: 2 fresh potatoes/day peeled, cooked and cooled before consumption, 2 bananas/day, 1 apple/day peeled.
	Permitted	Protein-rich foods: 100–150 g of fresh white fish once a week as a substitute for chicken. Carbohydrate-rich foods: white rice (unlimited), rice noodles without preservatives (unlimited), rice flour for baking (unlimited). Fruits: 1 avocado/day (no more 1/2 avocado per meal), 5 ripe strawberries/day, 1 cantaloupe slice/day. Vegetables: 2 tomatoes/day (or 6 cherry tomatoes), 2 cucumbers/day peeled, 1 carrot/day, fresh spinach (225 g raw leaves/day), 3 lettuce leaves once a day. Condiments: olive oil, canola oil, salt, pepper, paprika, cinnamon, cumin, turmeric, mint, oregano, coriander, rosemary, sage, basil, thyme, dill, parsley, onion (all types), garlic, ginger, natural lemon juice, honey (3 tbsp/day), sugar (3 teaspoons/day). Drinks: water, sparkling water, infusions, 1 glass of freshly squeezed orange juice per day.

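### Section 2.12 does not extend masking to rectus femoris ultrasound, which the article itself names as a possible source of measurement bias

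*Protocol article*

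**What the plan says.** **Blinding.** Section 2.12 sets a default: "Due to the nature of the intervention, neither patients nor research or medical staff will be blinded". It then makes two exceptions in order to limit bias. One is "the clinicians from the Gastroenterology Department responsible for performing imaging assessments"; the other is the group of translational researchers who analyse the biological samples. Patients learn their arm when they accept participation, and Table 1 places consent before the baseline visit.

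**Role of muscle ultrasound.** The primary objective (Section 2.1) is to "determine the effectiveness and impact on body composition of implementing an ED for symptomatic remission in adult patients with active CD". The second specific aim, on the incidence of sarcopenia, relies on "assessment of muscle strength, function, and composition using functional tests, dynamometry, bioelectrical impedance analysis (BIA), and nutritional ultrasound". The Abstract ties the expected gain in lean mass and fall in visceral fat to BIA.

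**How the article classes it.** Section 2.13.1 groups nutritional ultrasonography with dynamometry and BIA as tests of function, and uses the language of radiological imaging for MR enterography and intestinal ultrasound. In Table 1, "Nutritional ultrasound" has its own row, apart from intestinal imaging.

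**Admitted weakness.** The limitations in the Discussion include "both inter- and intra-observer variability in ultrasound assessments, including intestinal ultrasound and quadriceps rectus femoris muscle evaluation" as a further possible source of measurement bias.

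**The concern.** The article treats two ultrasound measures as dependent on the observer. Section 2.12 plainly protects the intestinal one and does not mention the muscle one. If muscle ultrasound follows the default rule, the person who places the calipers can know the arm and the visit.

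Observer variability that is unrelated to arm mostly adds noise and costs power. Variability in an operator who knows the arm can shift readings in one direction. A two-sample comparison cannot tell such a shift from a real change in muscle, and a larger sample does not remove it. What is at stake is the credibility of one of the muscle measures reported for body composition and sarcopenia.

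**Working it through.** **1. Is muscle ultrasound covered by the masking?** Three places bear on this.
- Section 2.12: "neither patients nor research or medical staff will be blinded" is the rule, and only imaging by Gastroenterology and the laboratory work are exempt.
- Section 2.13.1: muscle ultrasound is a test of function, while imaging means the bowel examinations.
- Table 1: muscle ultrasound and intestinal imaging are separate rows on different schedules. Muscle ultrasound is also done at 12 weeks; intestinal imaging is not.

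Read together, they put muscle ultrasound under the default rule. No section says who performs it, so this is an inference from the wording.

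**2. The plan's own sample size.** Section 2.11 gives 48 per group at a significance level of 0.05 and power of 0.8, with no effect size, so the figure cannot be reproduced directly. Solving backwards for two means (two-sided, 1:1):

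detectable difference = (1.960 + 0.842) × √(2/48) = 0.572 SD.

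Dropout: 48 / 0.95 = 50.5, rounded up to 51, which lies inside the stated 50–55.

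**3. What an arm-related drift would do.** Let d be the difference between arms in mean reading error, in SD units, with no true effect. The documents give no value for d; those below are assumed. The two-sample t statistic then follows a noncentral t distribution with 94 degrees of freedom and noncentrality d × √(48/2) = 4.899d. The false-positive rate is the probability that it exceeds the two-sided critical value in either direction. The 0.01 column is Section 2.15's Bonferroni rule with five comparisons (0.05/5); the number five is assumed, because the article gives none.

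| Assumed drift d (SD) | Noncentrality | Rate at 0.05 | Rate at 0.01 |
|---|---|---|---|
| 0 | 0 | 5.0% | 1.0% |
| 0.1 | 0.49 | 7.7% | 1.9% |
| 0.2 | 0.98 | 16.3% | 5.4% |
| 0.3 | 1.47 | 30.7% | 12.9% |

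The normal approximation gives 7.8%, 16.5% and 31.2% at 0.05 for the three drifts. With 55 per group, a drift of 0.2 SD gives 18.0% at 0.05. A drift of 0.3 SD is about half of the detectable difference (0.3 / 0.572 = 0.52).

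**4. Number of images.** Assume one still per scan and no dropout. Table 1 schedules four scans (baseline, 12, 24 and 48 weeks): 2 × 50 × 4 = 400 to 2 × 55 × 4 = 440. Section 2.10 also places nutritional ultrasound at 6 weeks, which makes five scans: 2 × 50 × 5 = 500 to 2 × 55 × 5 = 550.

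**The case against.** - **The operator is not named.** A reader might infer that muscle ultrasound is definitely measured by staff who know the arm. The article does not say so. Section 2.7 to 2.12 never assign the scan to a service; Section 2.3 says only that the Endocrinology and Nutrition Service recruits. The Section 2.12 exception is not limited in words to the bowel, and the Discussion mentions both ultrasound types together. This stands as a caution. The separate Table 1 rows and the classification in Section 2.13.1 still favour the reading that muscle ultrasound is not covered.
- **The primary objective does not rest on this measure.** A reader might infer that the whole body-composition half is compromised. It is not: BIA is the measure named for lean mass, and ultrasound is one of several tools under the sarcopenia aim. This stands and narrows the point.
- **The limitation concerns variability, not drift by arm.** This also stands. The article concedes observer variability and calls it potential bias, but offers no evidence that readings would move with allocation.
- **The figures are illustrative.** The drifts are assumed, 0.1 SD does little, and the 0.05 column ignores the planned Bonferroni correction. With the correction the absolute rates fall, but a 0.2 SD drift still gives about five times the nominal 1%.
- **An article condenses the full protocol.** Reading procedures may be set out elsewhere. However, Section 2.12 states who is masked and who is not, so the scope of masking is fixed here, and it omits a measure that the same article calls vulnerable.

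**Conclusion.** The point holds in a limited form. On the natural reading of Sections 2.12 and 2.13.1 and Table 1, rectus femoris ultrasound is left unmasked, while the Discussion names it as a possible source of measurement bias. This affects one of several body-composition and sarcopenia measures. It allows a bias toward one arm and does not show that one will occur.

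The size depends wholly on the assumed drift: negligible inflation if there is none, mild at 0.1 SD, and serious from about 0.2 SD upward, with or without the Bonferroni correction. The calculation further assumes a two-sided t-test, 48 analysed per arm and no true effect. It is worth correcting because the remedy is cheap and must be in place before scans accrue: images that were not saved cannot be read again.

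**What to change.** State in Section 2.12 that measurement of muscle ultrasound is masked, and describe the procedure in Section 2.13.1:
- Save the rectus femoris stills at every scheduled scan.
- An existing team member who does not measure them assigns a code that hides participant, arm and visit.
- After the last week-48 scan, the usual operator measures all stills in random order in one batch.
- That coded reading is the study value for comparisons between arms.

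If the imaging exception was already meant to include muscle ultrasound, Section 2.12 should say so in a sentence. Section 2.10 and Table 1 should also be reconciled on whether a 6-week scan takes place, since this sets the number of images.

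Cost: no new scan, visit or reader. Someone already on the team must do the coding, and the operator must read 400–440 images, or 500–550 with week 6. Coded reading does not remove bias that enters while the image is being acquired, for example through probe pressure. That limit should stay in the Discussion.

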### 2.7. Consent

Before any study-specific tests or procedures are performed, patients who meet the participation criteria (or their witness or legal representative) will be asked to sign the informed consent document approved by the Ethics Committee. They will be given sufficient time to review the informed consent document and have their questions answered before signing.

Each individual will be informed both orally and in writing about the study methodology, as well as about the potential adverse effects that may occur as a result of the various assessments to be carried out. Similarly, they will be informed that participation in the study is voluntary, both in terms of joining the study and of withdrawing from it at any time. In addition, all participants will be made aware of the characteristics of the products they will be consuming and the possible adverse effects that may occur during their use. Each participant will sign an informed consent form for participation in the project and an additional one for each stress test performed.

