### 2.10. Intervention

Upon consenting to participate, patients will be randomized into two study arms based on the intervention administered:Control Group: Patients will receive modifications to their pharmacological treatment alongside standard nutritional recommendations. The control group will follow a Mediterranean diet with increased caloric and protein intake during the acute flare. The diet will emphasize a balanced nutritional intake without unnecessary food restrictions, along with adequate fiber and hydration (as tolerated), and a reduction in ultra-processed food consumption.Experimental Group: Patients will receive modifications to their pharmacological treatment and will be assigned to an intervention consisting of an exclusion diet in conjunction with supplemental enteral nutrition. This nutritional strategy will involve a progressive increase in the caloric intake derived from the diet, coupled with a corresponding reduction in supplemental enteral nutrition.

Prior to initiating the nutritional intervention—and subsequently at 6 and 12 weeks after the onset of the diet—alterations in body composition and functionality will be evaluated through anthropometric measurements and biochemical parameters pertinent to both the underlying pathology and the overall health status of the patient. Comprehensive functional assessments, including dynamometry and additional analyses such as BIA and nutritional ultrasound, will be conducted. Furthermore, a detailed nutritional and morphofunctional evaluation will be performed 24 and 48 weeks after the initiation of the exclusion diet [Figure 1].

Baseline biological samples (blood, urine, and stool specimens) will be collected before the start of the nutritional intervention. During the intervention, additional collections will occur at the 6-, 12-, 24-week visits, with a final sample collection at 48 weeks. A detailed assessment schedule can be found in Table 1.

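### Patients learn their arm at consent, before the t0 baseline assessments, so self-reported, effort-dependent and staff-measured baselines are taken unblinded; the promise that prescribing is independent of the diet has no stated safeguard

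*Protocol article*

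**What the plan says.** On allocation, section 2.10 states: "Upon consenting to participate, patients will be randomized into two study arms". Section 2.12 adds that eligibility comes first: "Patients will be randomized in a 1:1 ratio after meeting the study inclusion and exclusion criteria". The same section gives the time of disclosure: "Group assignment will be disclosed to patients at the moment of their participation acceptance". It also says that patients, research staff and medical staff are not blinded. The exceptions are the gastroenterology clinicians who perform imaging and the researchers who analyse blood, urine and stool.

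On consent, section 2.7 begins "Before any study-specific tests or procedures are performed, patients who meet the participation criteria" and goes on to say that these patients are asked to sign the consent form. Table 1 marks the signature only in the Pre-DE column, together with the diagnostic HBI and MUST.

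On baseline, the Table 1 footnote defines "t0: baseline or initial visit". In that column the table marks CVEII-9, HBI, 24 h recall, FFQ, SARC-F, dynamometry, BIA, nutritional ultrasound, biological samples and intestinal imaging. Sections 2.10, 2.13.1 and 2.13.2 require baseline collection to precede the start of the diet. None of them requires it to precede allocation.

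On the drug, section 2.2 says: "The pharmacological treatment will be prescribed based on clinical indications by the medical team at baseline". The sentence continues with a commitment that the diet allocation will not affect this choice. Section 2.2 also says that patients enter when a start or change of drug is already planned.

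**The concern.** A baseline value is a neutral reference only if it cannot depend on the arm. Here a patient who already knows the allocation completes the quality-of-life questionnaire, recalls diet and performs the grip test. Staff who also know it record the HBI and take the body-composition measurements. A patient told to follow the exclusion diet may also change eating habits before the t0 stool sample, and blinded laboratory analysis cannot undo that.

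The primary objective in section 2.1 includes impact on body composition, and the specific aims cover muscle strength, quality of life and the progression of clinical and body-composition parameters. Section 2.2 describes the data as matched. Baseline values are therefore likely to enter these comparisons, although section 2.15 does not say in what form.

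The drug raises a second, separate question. Every participant starts or changes one, so it is a competing explanation for any difference in outcome. The commitment in section 2.2 is the right principle. However, the medical staff are unblinded, and no step fixes a record of the intended treatment before the arm is known. A reader of the results could not verify that the commitment was kept.

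**Working it through.** **Order of events.**

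1. Eligibility is confirmed and consent is signed (2.3, 2.7; Table 1, Pre-DE).
2. Randomisation follows on consent and eligibility (2.10, 2.12).
3. The arm is disclosed at acceptance of participation (2.12).
4. The t0 assessments and samples are taken (Table 1). They are tied only to the start of the diet (2.10, 2.13.1, 2.13.2).
5. The diet starts.

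Step 3 precedes step 4 as written. The drug is prescribed at baseline (2.2), but no section places that decision before or after steps 2 and 3.

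**Which measures are exposed.** Exposed: t0 CVEII-9, t0 HBI, 24 h recall, FFQ, SARC-F, dynamometry, BIA and nutritional ultrasound, plus the content of the stool sample if diet changes early. I read the imaging exception in 2.12 as covering intestinal imaging; the article does not say who performs nutritional ultrasound. Not exposed, or less so: the Pre-DE HBI and eligibility marker, laboratory analysis and intestinal imaging. Remission is HBI below 5 and calprotectin below 250 µg/g (2.13.1). These are absolute thresholds, so a shifted baseline does not enter directly.

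**Illustrative size, baseline.** The plan states no figure to reproduce. Inputs: n = 48 per arm and level 0.05 (2.11), taken as two-sided. Assumed: no true diet effect, an arm-related shift d in the t0 value (in SD units) that does not carry over to follow-up, and a baseline–follow-up correlation r.

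- Change score: bias d; SE = √(2(1 − r)) × √(2/48).
- Baseline-adjusted: bias r × d; SE = √(1 − r²) × √(2/48).
- Type I error = 1 − Φ(1.96 − bias/SE) + Φ(−1.96 − bias/SE).

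Example, d = 0.2 and r = 0.5. Change score: SE = 1 × 0.204, bias/SE = 0.98, type I error 16.5%. Adjusted: bias 0.10, SE = 0.866 × 0.204 = 0.177, bias/SE = 0.57, type I error 8.7%.

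| d (SD) | r | Change score | Baseline-adjusted |
|---|---|---|---|
| 0.1 | 0.3 | 7.0% | 5.3% |
| 0.1 | 0.5 | 7.8% | 5.9% |
| 0.1 | 0.7 | 9.7% | 7.7% |
| 0.2 | 0.3 | 13.1% | 6.1% |
| 0.2 | 0.5 | 16.5% | 8.7% |
| 0.2 | 0.7 | 24.4% | 16.1% |
| 0.3 | 0.3 | 23.7% | 7.5% |
| 0.3 | 0.5 | 31.2% | 13.6% |
| 0.3 | 0.7 | 47.5% | 30.2% |

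Adjustment reduces the problem but does not remove it.

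**Illustrative size, drug.** This applies only if drug choice did differ by arm. Bias in the remission difference = difference in drug share × difference in remission between drugs. With both assumed at 10 to 30 points, the bias runs from 0.10 × 0.10 = 1 point to 0.30 × 0.30 = 9 points. Taking 45% remission on the less effective drug (also assumed) and 48 per arm, the type I error runs from 5.1% to 14.7%. For a 20-point share difference and a 30-point drug difference, the arms have 63% and 57% remission: bias 6 points, SE = √(2 × 0.60 × 0.40/48) = 0.10, type I error 9.2%.

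**The case against.** The strongest reply is that the exposure is narrow. An HBI exists from before allocation, laboratory and intestinal imaging readers are blinded, and remission does not depend on the baseline value. Table 1 gives no interval between Pre-DE and t0, so the gap may be short. All of this stands and confines the point to the exposed t0 measures. A short interval does not remove it, because knowing the arm for an hour is enough to colour a questionnaire or a grip test.

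A reader might infer that unblinded staff choose the drug after seeing the allocation. The documents do not show that. Patients enter with a start or change already planned, the choice is stated to follow clinical indication independently of the diet, and prescribing at baseline is not the same as prescribing after allocation. What stands is that the commitment has no stated safeguard. The direction of any bias is also unknown, since prescribers could equally compensate the control arm.

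A reader might also infer that patients who leave after disclosure contribute no baseline data. That is not so: HBI, MUST and the eligibility data already exist, and section 2.5 retains data collected up to withdrawal. They would lack only the t0 measures.

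Finally, one might fault simple randomisation by a site team member. Simple randomisation is legitimate at this sample size, and the chance imbalance it allows is covered by the nominal error rate. Concealment procedures are detail that an article commonly leaves to the full protocol. Neither is part of this point.

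**Conclusion.** The point holds in a limited form and should be fixed. The plan as written gives patients their arm before the t0 assessments, so body composition, strength, quality of life and dietary intake have unblinded baselines, and early diet change could reach the t0 stool sample. Comparisons using change from baseline or baseline adjustment can be biased. The type I error range of 5.3% to 47.5% across both analyses shows what is possible under the assumed shifts and correlations, not what will happen. The range does not apply to comparisons of follow-up values alone, and the remission endpoint is not directly affected.

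On co-treatment, the conclusion is only that the independence commitment in section 2.2 cannot be verified. The bias of 1 to 9 points is conditional on assumed differences in drug use and drug effect that the documents neither state nor imply.

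**What to change.** In sections 2.10 and 2.12 and in Table 1, set one order:

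1. consent and eligibility;
2. all t0 assessments and samples;
3. the intended drug treatment recorded in the eCRF;
4. allocation generated and disclosed;
5. diet started.

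Step 3 is a record only and puts no constraint on what is prescribed, then or later. In sections 2.10, 2.13.1 and 2.13.2, tie baseline to the time before allocation as well as before the diet. Report drug use by arm, so that the commitment in section 2.2 can be checked.

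The cost is that patients learn their arm slightly later and the eCRF gains one entry. The change cannot be applied retrospectively to patients already randomised. If there are any, record for each whether t0 followed disclosure.
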